# LIST OF ABBREVIATIONS AND RELEVANT DEFINITIONS

| **ApoA-I** | Apolipoprotein A-I |
| --- | --- |
| **ApoB48** | Apolipoprotein B48 |
| **ABCA1** | ATP binding cassette transporter 1 |
| **CCMO** | Central Committee on Research Involving Human Subjects |
| **CHD** | Coronary Heart Disease |
| **CV** | Curriculum Vitae |
| **FMD** | Flow mediated vasodilatation |
| **HDL-C** | High-density lipoprotein cholesterol |
| **hsCRP** | High-sensitive C-reactive protein |
| **IL-6** | Interleukin-6 |
| **LDL-C** | Low-density lipoprotein cholesterol |
| **MCP-1** | Monocyte chemotactic protein-1 |
| **METC** | Medical research ethics committee (MREC); in Dutch: medisch ethische toetsing commissie (METC) |
| **PPAR** | Peroxisome proliferator-activated receptor |
| **PWV** | Pulse wave velocity |
| **(S)AE** | (Serious) Adverse Event |
| **sE-Selectin** | Soluble E-Selectin |
| **sICAM-1** | Soluble Intercellular adhesion molecule 1 |
| **VCAM-1** | Vascular cell adhesion molecule 1 |
| **Sponsor** | The sponsor is the party that commissions the organisation or performance of the research, for example a pharmaceutical company, academic hospital, scientific organisation or investigator. A party that provides funding for a study but does not commission it is not regarded as the sponsor, but referred to as a subsidizing party. |
| **TAG** | Triacylglycerol |
| **TCH** | Total cholesterol |
| **WMO** | Medical Research Involving Human Subjects Act (Wet Medisch-wetenschappelijk Onderzoek met Mensen |

#

# SUMMARY

**Rationale**: A substantial residual cardiovascular risk is still present, despite successful efforts to lower atherogenic serum low-density lipoprotein cholesterol (LDL-C) concentrations. An additive strategy may be raising high-density lipoprotein (HDL) concentrations, and in particular those of its major protein constituent apolipoprotein A-I (apoA-I). Based on cell and animal studies, resveratrol may be a promising candidate in this respect. Effects of this dietary component on apoA-I has however never been evaluated in a placebo controlled human intervention study.

**Objective**: To evaluate the effects of resveratrol on apoA-I concentrations in subjects with low serum HDL-cholesterol (HDL-C) concentrations at baseline. Minor objectives are to study the effects of resveratrol on (1) endothelial function and arterial stiffness as measured by flow mediated vasodilatation (FMD) and pulse wave velocity (PWV) during the fasting and postprandial phase (2) endothelial function of the retinal vasculature (3) lipid and glucose metabolism during the fasting and postprandial phase, and (4) biomarkers for low-grade systemic inflammation (interleukin-6 (IL-6), C-reactive protein (CRP)) and endothelial function (monocyte chemotactic protein-1 (MCP-1), sE-selectin, soluble intercellular adhesion molecule 1 (sICAM-1), and soluble vascular cell adhesion molecule-1 (sVCAM-1)).

**Study design**: A randomized, double-blind, placebo controlled cross-over design. The total study duration will be 12 weeks, consisting of a 4 weeks experimental period, a 4 weeks wash-out and a 4 weeks control period.

**Study population**: Fifty overweight and obese men and women, aged 45-70 years, with low HDL-C concentrations (men <1.0 mmol/L and women <1.3 mmol/L).

**Intervention**: During the experimental period, subjects will receive daily one capsule at lunch and one capsule at dinner, each providing 75 mg resveratrol. During the control period, subjects will receive daily two placebo capsules, each containing 58 mg cellulose.

**Main study parameters/endpoints**: Measurements will be performed at the start and end of each 4-week intervention period. Effects of resveratrol supplementation will be calculated as the absolute differences between values obtained at the end of each period. The primary endpoint is the change in serum apoA-I concentrations.

**Nature and extent of the burden and risks associated with participation, benefit and group relatedness**: Before the study, subjects will be screened to determine eligibility during two visits of respectively 15 and 10 minutes. During these visits, body weight, height and blood pressure will be measured. In addition, a venous blood sample (5.5 mL at each occasion) will be drawn. During the study, subjects will receive the control and resveratrol capsules in random order. At days 1, 25, and 28 of each 4 wk experimental period, a fasting blood sample will be drawn (2 x 10 mL and 4 x 16.5 mL). In addition, a 4 hr postprandial test will be performed at day 28 of each experimental period. For this, subjects will receive two muffins and 300 mL low-fat milk, and an additional 8 blood samples will be taken (80 mL at each test). Thus, in total 257 mL blood will be drawn. Before and after each postprandial test, two FMD (including an ECG) and two PWV measurements will be performed. During the last week of each intervention period, a retinal image will be taken on a separate occasion. Subjects will be asked to fill out a food frequency questionnaire two times and to keep a study-diary throughout 12 weeks. On rare occasions, blood sampling might cause bruises or hematoma. Total time investment for the subjects will be approximately 16 hours.

# 1. INTRODUCTION AND RATIONALE

Despite aggressive treatment regimens to lower atherogenic low-density lipoprotein cholesterol (LDL-C) concentrations below 2.6 mmol/L, there is still a substantial residual cardiovascular risk. A wealth of evidence from in vitro and in vivo studies, however, shows that raising high-density lipoprotein cholesterol (HDL-C) or apolipoprotein A-I (apoA-I) concentrations protects against coronary heart disease (CHD). For example, increasing serum apoA-I and/or HDL-C concentrations by intravenous infusion of recombinant apoA-I Milano / phospholipid complexes rapidly reduced atheroma-volume in patients with acute coronary syndromes (1). Also, selective delipidation of plasma HDL (converting large HDL-particles to small pre-beta HDL-particles, thereby increasing the relative amount of apoA-I) enhanced reverse cholesterol transport in vivo in African Green monkeys (2). This suggests that increasing apoA-I concentrations may be even more beneficial than simply increasing the HDL-C pool. In addition, apoA-I protein may have anti-inflammatory, antioxidant, and anti-thrombotic effects, which may even enhance its cardioprotective effects (3-5). In fact, a special working group already emphasized in 2001 the need to develop interventions to raise HDL-C or apoA-I (6). However, despite many initiatives, we have to admit that 9 years later no new widely applicable intervention strategies with proven efficacy have been developed. This is even more worrisome since the number of subjects with obesity, type II diabetes and the metabolic syndrome - for which dyslipidemia (low HDL-C and high triacylglycerol) is an important clinical hallmark - has increased steadily. Therefore, there is strong need to better understand possibilities to intervene with apoA-I and HDL synthesis.

Epidemiological studies have now shown that a higher polyphenol intake is associated with a reduced cardiovascular risk (7, 8). This association may be due to increased intakes of resveratrol, a polyphenol found in food items such as red wine and grapes. It has been found that resveratrol influences numerous mechanisms, which act on the progression as well as on the regression of atherosclerosis (9). In fact, in hyperlipidemic genetically modified animal models, resveratrol-enriched diets suppressed lesion formation (10, 11). In addition, human intervention studies showed a HDL-C elevating effect of berries (12) and red wine (13), both of which contain resveratrol. The amount of resveratrol in the diet is low. Concentrations in red wine, for example, vary from undetectable to 14.3 mg/L (14). Resveratrol however is safe and no serious adverse events were noted after single oral doses of 1, 2.5 or 5 g resveratrol in humans (15).

The production of apoA-I, the predominant apoprotein in HDL particles is under direct PPAR alpha transcriptional control. The positive effects of fibrates - known PPARalpha ligands - on serum apoA-I and HDL-C concentrations are also ascribed to their PPAR alpha activating potential (16). In this respect, it is an important finding that resveratrol can elevate the activity of the transcription factor PPAR alpha, a finding that has been patented (17, 18). In this patent, it is described that in vitro resveratrol increases apoA-I production via PPAR alpha activation. By using the newly developed drug RVX-208, a resveratrol derivate, which is based on this patent and targets de novo apoA-I production, a significant increase in serum apoA-I concentrations, predominantly in the pre-beta HDL fraction was shown in African Green monkeys (19). Importantly, also the cholesterol efflux from cholesterol loaded macrophages towards the HDL fraction via the ABCA1 pathway was improved. As far as we know, these effects have not been studied in humans. We therefore propose to evaluate, in a placebo controlled double-blind human intervention study, the effects of resveratrol in subjects with low serum HDL-C concentrations on changes in serum apoA-I and HDL-C (subfraction) concentrations. Moreover, we will also examine functional effects due to resveratrol supplementation by measuring the capacity of the vessels to respond to a standardized fat-load during the postprandial period by measuring flow-mediated vasodilatation (FMD) of the brachial artery and arterial stiffness by pulse wave velocity (PWV). Noteworthy, with the first technique it has earlier been shown that infusion of HDL improved endothelial function (20).

# 2. OBJECTIVES

Considering the background information given in the previous paragraph, the following research questions are formulated:

**Primary research question:**

What is the effect of resveratrol supplementation on serum apoA-I concentrations in men and women with low HDL-C concentrations?

*Major null hypothesis, H_0_:*

As compared with control capsules, a daily intake of two capsules each containing 75 mg resveratrol for 4 weeks does not change serum apoA-I concentrations in subjects with low HDL-C concentrations.

*Major alternate hypothesis, H_a_:*

As compared with control capsules, a daily intake of two capsules each containing 75 mg resveratrol for 4 weeks does change serum apoA-I concentrations in subjects with low HDL-C concentrations.

**Secondary research questions:**

1. What is the effect of resveratrol supplementation on FMD and PWV during the fasting and postprandial phase?
2. What is the effect of resveratrol supplementation on retinal microvasculature, measured as AV-ratio and vessel diameter from digitized analogue fundus photographs?
3. What is the effect of resveratrol supplementation on lipid (apoB, total cholesterol, LDL-cholesterol, HDL-C and triglycerides) and glucose (glucose and insulin) metabolism during the fasting and postprandial phase?
4. What is the effect of resveratrol supplementation on serum biomarkers for low-grade systemic inflammation (hsCRP, IL-6) and endothelial function (sICAM-1, VCAM-1, MCP-1 and sE-Selectin)?

# 3. STUDY DESIGN

A randomized, double-blind, placebo-controlled cross-over study will be carried out, as outlined in Table 1.

**Duration of the study**

It is projected that the study will start October 1, 2010. It is expected that the last subject will finish the study June 30, 2011.

Each subject will be involved in the study for 14 weeks:

- 1-2 weeks screening before enrolment
- First period: 4 weeks
- Wash-out period: 4 weeks (21, 22)
- Second period: 4 weeks

Table 1: Experimental design

|  | Screening | | Intervention period | | | Wash-out period | Intervention period | | |
| --- | --- | --- | --- | --- | --- | --- | --- | --- | --- |
| Group 1 (N=25) |  | | Experimental capsules | | |  | Placebo capsules | | |
| Group 2 (N=25) |  |  | Placebo capsules | | |  | Experimental capsules | | |
| Week |  | | 1 | 4 | | 4 weeks | 9 | 12 | |
| Day |  |  | 0 | 25 | 28 |  | 56 | 81 | 84 |
| Visit | -2 | -1 | 1 | 2 | 3 |  | 4 | 5 | 6 |
| Blood sampling | X | X | X | X | X |  | X | X | X |
| Postprandial test |  |  |  |  | X |  |  |  | X |
| Flow mediated dilation, including ECG |  |  |  |  | XX |  |  |  | XX |
| Pulse wave velocity |  |  |  |  | XX |  |  |  | XX |
| Retinal images * |  |  |  | X | |  |  | X | |
| Body weight | X | X | X | X | X |  | X | X | X |
| Height | X |  |  |  |  |  |  |  |  |
| Blood pressure,  heart rate | X | X | X | X | X |  | X | X | X |
| Capsule count |  |  |  | X | X |  |  | X | X |
| Food intake |  |  |  |  | X |  |  |  | X |
| Study diary |  |  | During total study period |  |  |  |  |  |  |
| AE reporting |  |  | During total study period | | | | | | |

* At an extra visit during the last week of each experimental period

Before screening, subjects will be informed about the procedures and informed consent will be obtained. Subjects will be informed about their results and advised to consult their general practitioner when values are outside normal ranges. When a subject does not want to be informed about the results, it is not possible to participate in this study. Subjects that fulfil all inclusion criteria and are willing to participate will be randomly allocated to receive either the placebo capsules or the experimental capsules for a period of four weeks. This period will be followed by a four-week wash-out period, after which regimes will be crossed over. In this way variation due to drift of variables with time is eliminated. Possible residual effects will be minimized by a washout period of at least four weeks between two periods. The placebo and experimental capsules have to be consumed at lunch and dinner, and will be coded to assure blindness of the investigator and participants. Experimental capsules will each contain 75 mg resveratrol and placebo capsules 58 mg cellulose (**Appendix 1**). During each visit, subjects will be supplied with the amount of capsules that is sufficient for the next visit. Leftovers should be returned and counted.

During the study, subjects will record in diaries any signs of illness, medication used, menstrual phase and any deviations from the protocol. Subjects are asked not to change their dietary habits, except for stopping the use of resveratrol-containing products during the study. Subjects will receive a list in which the resveratrol-containing products are stated, examples are wine, grapes and berries. Furthermore, subjects will be asked to maintain their level of physical exercise and use of oral contraceptives. At the end of each intervention period, food intake will be assessed by a validated food frequency questionnaire. Fasting blood samples will be drawn before the start of the study (day 0), twice in week 4 (days 25 and 28), after 8 weeks (day 56) and twice at the end of the study (days 81 and 84). FMD and PWV measurements will be performed at the end of each four-week intervention period (days 28 and 84), before and 4 hours after a standardized fat-load. During these days, blood will be sampled as indicated in figure 1 and as further explained in paragraph 6.2. Furthermore, retinal images will be made during the last week of each experimental period (see paragraph 6.3.2 and 6.3.3). Body-weight, height, blood pressure and ECG will be recorded as indicated in Table 1.

# 3. STUDY POPULATION

## 3.1 Population

Men and women, aged between 45 and 70 years, will be recruited. The lower limit for age is set at 45 years, because from experiences in the past it became clear that the major part of people aged under 45 will not meet the inclusion criteria as formulated in §3.2. The upper limit for age is set at 70 years, because from our previous experience a large proportion of people aged over 70 years will not meet the inclusion criteria as formulated in paragraph 4.2. Because we do not want to encumber these subjects unnecessarily, we have decided to set the lower limit for age at 45 years and the upper limit at 70 years.

## 3.2 Inclusion criteria

Subjects are asked to fill out a general health questionnaire in between the first and second screening visit. Only healthy subjects will be included. The inclusion criteria are:

- aged between 45 and 70 years
- HDL-C <1.21 mmol/L (men)
- HDL-C <1.53 mmol/L (women)
- serum total cholesterol <8.0 mmol/L
- plasma glucose <7.0 mmol/L
- BMI between 25 – 35 kg/m^2^
- non-smoking
- willingness to abstain from resveratrol rich products from two weeks prior to the study and the duration of the study:
  - grapes
  - wine (red and white)
  - all berries
  - peanuts
  - peanut butter
  - soy (products)
  - pomegranate
  - grape juice
  - port wine

## 3.3 Exclusion criteria

The exclusion criteria are:

- unstable body weight (weight gain or loss >3 kg in the past 3 months)
- any medical condition requiring treatment and/or medication use
- indication for treatment with cholesterol-lowering drugs according to the Dutch Cholesterol Consensus
- use of medication or a medically-prescribed diet known to affect serum lipid or glucose metabolism. The use of oral contraceptives and paracetamol is allowed.
- Active cardiovascular disease (for instance congestive heart failure) or recent (<6 months) event, such as acute myocardial infarction or cerebro-vascular accident
- not willing to stop the consumption of vitamin supplements, fish oil capsules or products rich in plant stanol or sterol esters 3 weeks before the start of the study
- men: consumption of >21 glasses of alcohol-containing drinks per week

women: consumption of >14 glasses of alcohol-containing drinks per week

- abuse of drugs
- pregnant or breastfeeding women
- participation in another biomedical study within 1 month prior to the screening visit
- having donated blood (as blood donor) within 1 month prior to the screening visit, planning to donate blood during the study or within one month after finishing the study
- impossible or difficult to puncture as evidenced during the screening visits

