# 5. METHODS

## 5.1 Study procedures

Subjects will come to the department twice for screening visits. During the first screening visit, the subjects will be weighed, blood pressure will be determined in four-fold (the first measurement will be discarded and the last three measurements will be averaged), body height will be determined, and a venous blood sample (5.5 mL) will be drawn for analysis of plasma lipids and glucose concentrations. During the second screening visit, body weight and blood pressure will be determined again and a second venous blood sample (3.5 mL) will be drawn for analysis of plasma lipids and glucose concentrations. Two screening visits are planned to reduce the within-subject variability in the parameters of interest.

On the day preceding the test day, subjects will be asked to avoid high fat foods, alcohol, caffeine and taking part in any strenuous activity/exercise (as these may influence lipid metabolism or other outcomes measures in the short-term). Subjects will be asked to fast overnight and will be instructed to avoid eating or drinking anything, except water, after 8 pm. Subjects will arrive at around 8.00 AM the following morning. Flow-mediated vasodilatation and pulse wave velocity measurements will be performed, a venous cannula (fixed needle) will be inserted and a fasting blood sample will be collected. During the FMD measurement, and ECG will be performed. Subjects will then consume the muffins and low-fat milk within 10 minutes. Further venous blood samples will be collected at regular intervals for up to 4 hours postprandially. During the 4 hours of the study, subjects will refrain from the consumption of any food or drink except water, which they will be asked to consume at regular intervals.

All venipunctures will be performed as much as possible by the same technician, at the same location, and at the same time of the day. Serum or plasma will be obtained by low-speed centrifugation and stored as appropriate. When possible, samples from one subject will be analyzed within one run at the end of the study under strict quality control. The blood-sampling scheme is given in Table 4.

The total amount of blood drawn will be 329 mL (5.5 mL during the two screening visits, 34.5 mL at days 0, 25, 56 and 81 and 90 mL at days 28 and 84) per person during the whole study. Therefore, subjects are not allowed to have donated blood 8 weeks prior to participation.

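### Section 3.3 bars blood donors for 1 month before screening, section 5.1 for 8 weeks before participation, so a person can pass the exclusion list and still breach the protocol

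*Protocol*

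**What the plan says.** Protocol section 3.3 lists the exclusion criteria. One of them is "having donated blood (as blood donor) within 1 month prior to the screening visit". The same item also excludes people who plan to donate during the study or in the month after it.

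Section 5.1 sets a second limit. It states that "The total amount of blood drawn will be 329 mL", made up of "5.5 mL during the two screening visits, 34.5 mL at days 0, 25, 56 and 81 and 90 mL at days 28 and 84", and then draws the consequence: "Therefore, subjects are not allowed to have donated blood 8 weeks prior to participation".

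The interval between screening and day 0 comes from the Study Design section, under Duration of the study: "1-2 weeks screening before enrolment". The same place says "Each subject will be involved in the study for 14 weeks", which fits 12 weeks of study plus at most 2 weeks of screening.

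The 8-week limit does not appear in section 3.3. Section 5.1 does not mention the 1-month limit, and nowhere does the protocol define when participation begins.

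**The concern.** Both sentences restrict the same act, blood donation before the study, and both are current text. They give different lengths and count from different points. Section 3.3 presents itself as the exclusion criteria, so a person can be found eligible against that list and be forbidden by section 5.1. The result would be a protocol deviation at enrolment that no one working from section 3.3 would notice.

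The 8-week limit is also the one that the protocol justifies by its own blood draw. The restriction given a subject-protection reason is therefore the one missing from the list of exclusions. A reader who does find it cannot apply it uniformly, because its starting point is undefined.

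**Working it through.** **The plan's own volume figure.** Section 5.1 gives two screening draws of 5.5 mL, four draws of 34.5 mL and two test days of 90 mL:

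2 × 5.5 + 4 × 34.5 + 2 × 90 = 11 + 138 + 180 = 329 mL.

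The stated total reproduces.

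**The two donation windows.** Inputs: 1 month (section 3.3), taken as 28 to 31 days; screening lead of 1 to 2 weeks, or 7 to 14 days (Duration of the study); 8 weeks, or 56 days (section 5.1).

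| Start of participation | Reach of section 3.3 | Section 5.1 | Gap |
| --- | --- | --- | --- |
| Day 0 | 28 + 7 = 35 to 31 + 14 = 45 days | 56 days | 56 − 45 = 11 to 56 − 35 = 21 days |
| Screening visit | 28 to 31 days | 56 days | 56 − 31 = 25 to 56 − 28 = 28 days |

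For the windows to coincide at day 0, the screening lead would have to be 25 to 28 days. At most 14 are planned.

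**An example.** Someone who donated 35 days before screening passes section 3.3, since 35 exceeds 31. That person reaches day 0 at 35 + 7 = 42 to 35 + 14 = 49 days after donation. Both are short of 56, and so is 35 if the count stops at screening. Section 5.1 bars this person on either reading.

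**How much sampling falls inside 56 days.** Take the shortest interval that section 3.3 permits, with day 0 at about 35 to 45 days after donation.

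- Day 25 falls at 35 + 25 = 60 to 45 + 25 = 70 days.
- Day 28 falls at 35 + 28 = 63 to 45 + 28 = 73 days.

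Both are past 56 days, and the remaining visits are later still. Only the two screening draws and day 0 are inside: 2 × 5.5 + 34.5 = 45.5 mL, and 45.5 / 329 = 0.138, about 14% of the section 5.1 total.

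**Is the volume behind the 8-week rule settled?** It is not.

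- The Summary gives 2 × 5.5 + 2 × 10 + 4 × 16.5 + 2 × 80 = 11 + 20 + 66 + 160 = 257 mL, which matches its stated total but not the 329 mL in section 5.1.
- Section 4.2 gives 16.5 mL for the fasting sample and for each of seven later samples: 8 × 16.5 = 132 mL per test day, against 90 mL in section 5.1.
- Section 5.1 itself gives 3.5 mL for the second screening draw in its first paragraph. Using that, the total is 5.5 + 3.5 + 138 + 180 = 327 mL.

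These differences do not change the window arithmetic. They do mean that the reason given for the 8-week rule has no single figure behind it.

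**The case against.** The best defence is that the rules are nested. Anyone 56 days past donation at day 0 was at least 56 − 14 = 42 days past it at screening, and so also satisfies the 1-month rule. An investigator who follows the whole protocol applies both limits and breaks neither. The protocol does not say that eligibility is judged from section 3.3 alone. This is true, and it means that the rules can be obeyed together. It does not remove the conflict, because a section headed as the exclusion criteria still admits people whom another section forbids, and the start of the longer window is undefined.

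The defence is also right that the consequences are limited. A reader might infer that recent donors would be sampled repeatedly inside the forbidden window. The dates do not support this: from day 25 onward, every draw falls at least 60 days after donation, including both postprandial test days.

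A reader might also infer that day-0 haematology would still be recovering from the donation and so distort the safety baseline. The documents give no figure on recovery. Section 5.2.5 and its table only schedule haematology at the start and end of each period, and no comparison against day 0 is defined. That inference should not be drawn.

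**Conclusion.** The inconsistency is real and survives either reading of when participation starts. The gap is about 11 to 21 days if it starts at day 0 and 25 to 28 days if it starts at screening. These figures assume a month of 28 to 31 days and the planned screening lead of 7 to 14 days.

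The point concerns an eligibility limit tied to subject protection, and its practical reach is small. On section 5.1's volumes, about 45.5 of 329 mL would be drawn within 56 days of donation in the shortest-interval case. The documents do not allow an estimate of how many of the fifty subjects would fall in the gap.

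The primary apoA-I comparison (section 7.2) and the sample size (section 3.4) are unaffected. Nor do the documents settle which window is the intended one. It may be tempting to treat section 5.1 as correct because it gives a reason, but the blood volume on which that reason rests differs between sections.

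**What to change.** Reconcile sections 3.3 and 5.1 so that the same donation window, counted from the same defined reference point, appears in both. If the word participation is kept as the reference point, say which visit it means.

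In the same edit, reconcile the blood volumes: the 257 mL total in the Summary with the 329 mL in section 5.1; the 16.5 mL per postprandial sample in section 4.2 with the 90 mL per test day in section 5.1; and the 5.5 and 3.5 mL given within section 5.1 for the second screening draw. The donation rule will then rest on one stated total.

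The cost is a line of eligibility text and a few corrected figures. Depending on the window chosen, a few recent donors may be deferred or lost to recruitment. No analysis or sample-size text needs to change.
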